### ExerciseRx Intervention

#### Overview

The ExerciseRx platform was developed through a collaboration of investigators from the University of Washington Departments of Computer Science and Engineering and Human Centered Design and Engineering, and The Sports Institute at UW Medicine. It was designed to bridge the gap between consumer activity tracking devices, such as personal smartphones, and providers’ EHRs, thus making recommending physical activity possible as part of routine patient care. The ExerciseRx platform is a cloud-based, HIPAA-compliant, free digital platform that translates clinically relevant activity data collected by the patient’s existing personal smart devices (Android or iOS phone or tablet) into actionable metrics on a provider dashboard within the Epic EHR.

The ExerciseRx platform intervention protocol involves the following.

#### Baseline ExerciseRx Platform Onboarding Meeting With Research Coordinator

After completion of informed consent and the baseline measures, the research coordinator meets with the participant by Zoom (Zoom Communications, Inc) to help them download the ExerciseRx app to their smartphone. The coordinator then teaches them how to use the ExerciseRx app and instructs them to always carry their phone throughout the day. The coordinator reviews the ExerciseRx app procedures with the participant so that they know what to expect during the intervention period. The coordinator also educates the patient on how their step count, as tracked by the ExerciseRx app, is a key marker for physical activity. The coordinator reviews the recommended physical activity guidelines for adults with MS and resources for increasing physical activity and emails them a copy.

#### Baseline Step Count Period (1 Week)

Participants are asked to carry their phone throughout the day for 1 week to evaluate their baseline step count with no app interactions, notifications, or provider feedback during the baseline recording period. The baseline step count is used to calculate personalized step count goals.

#### Initial Personalized Daily Step Target

At the end of baseline, intervention participants receive a notification from the ExerciseRx app providing them with a personalized initial daily step target and weekly goal based on their baseline.

#### Exercise Progression and App Features

The ExerciseRx app displays a weekly step count goal, as well as daily step count targets (see Figure 2 for example). If participants meet their daily step targets, they are on track to meet their weekly step count goal. If 100% of the weekly goal is met the week before, the weekly step count goal increases by 3%. If 75%-99% of the goal is met, there is a 2% increase in their goal. If <75% of the weekly step count goal is met, there is no change to the weekly step count goal. The minimum step count is 1000 steps. The maximum goal in the ExerciseRx app is 10K and will not advance beyond that number, but since the step count is based on the patient’s baseline and progress, the patient may not reach 10K steps during the study period, as it is an individualized progression.

Participants use the app daily for 25 consecutive weeks after the baseline week. Weekly, participants complete an in-app survey of their individual barriers or facilitators to activity. During this period, the app displays daily step count targets, weekly step count goals, weekly summaries, a weekly assessment of barriers or facilitators to activity, semiweekly “Did you know” general and MS-specific messages such as “Exercise is medicine—increasing movement is a great way to better manage MS fatigue and may even reduce risk of relapse!” and provider automated feedback on activity progress (eg, thumbs-up reactions, weekly summaries, supportive messages, or encouragement based on whether the participant is near, at, or below their weekly goal).

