**Methods:**

Participants are ambulatory adults with MS (n=106) who engage in <150 minutes per week of moderate to vigorous intense physical activity. Enrolled participants are assigned to use the ExerciseRx app for 12 weeks, versus a waitlist, usual care control. Participants allocated to the intervention condition have access to the ExerciseRx app, and their providers have access to the participants’ activity data via a provider dashboard, connected to the EHR. Participants allocated to usual care receive the care they would normally obtain at the MS Center, including encouragement to participate in and increase physical activity as tolerated from their clinical provider and a handout that describes the current physical activity recommendations for adults with MS and links to local and web-based resources suitable for MS. The primary outcome is the change in average daily step count throughout the 12-week intervention. Secondary outcomes include symptoms (fatigue intensity, pain intensity, sleep, and depressive symptoms), patient-reported functional outcomes (physical functioning, fatigue interference, pain interference, falls, and social participation), and qualitative analysis of participant and provider interviews on usability and acceptability of the ExerciseRx platform.

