**Figure 2 figure2:**
[figure not shown]
The ExerciseRx app example screenshots.

This paper describes the rationale, aims, and protocol for the ExerciseRx-MS Trial, a randomized controlled trial designed to answer whether the ExerciseRx platform improves physical activity and other common symptoms and functional outcomes in adults with MS who are insufficiently active. The first aim is to evaluate the efficacy of the ExerciseRx platform relative to usual care in increasing physical activity, measured by average daily step count (primary outcome), activity volume, and the proportion who meet exercise guidelines in adults with MS who are insufficiently active. We hypothesize that participants randomized to the ExerciseRx app group will show a greater increase in physical activity at 12 weeks, as measured by daily average step count (primary outcome) and by total metabolic equivalent minutes of activity per week (secondary outcome) relative to participants randomized to usual care. We also hypothesize that a higher proportion of participants in the ExerciseRx app group will increase their minutes per week of moderate to vigorous intensity aerobic activity at 12 weeks (secondary outcome), relative to usual care participants.

The second aim is to evaluate the efficacy of the ExerciseRx platform relative to usual care on secondary outcomes, specifically symptoms (fatigue intensity, pain intensity, sleep, and depressive symptoms) and patient-reported functional outcomes (physical functioning, fatigue interference, pain interference, falls, and social participation). We hypothesize that participants in the ExerciseRx platform group will show greater improvements in secondary outcomes at 12 weeks relative to usual care participants. Additional secondary analyses will test maintenance of any treatment effects at a 3-month follow-up. We will also explore moderators of immediate (post-12 weeks) and 3-month follow-up outcomes, including demographics, disease course, and baseline participant factors (including fatigue, pain, depression, activity level, BMI, exercise self-efficacy, and disability) to explore potential moderators of treatment effects that can be evaluated a priori in future effectiveness and mechanistic research.

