## Methods

### Design

To address Aims 1 and 2, we are conducting a two-group parallel (1:1) assessor-masked randomized controlled trial designed to compare the ExerciseRx platform to usual care. We will use qualitative research methods to explore implementation factors (Aim 3). Outcomes are being collected at baseline, post a 12-week treatment period (primary end point), and at a 3-month follow-up after the treatment period. We selected a 3-month follow-up because it is feasible in a 3-year study and sufficient time to see a change in activity behavior. We preregistered the trial at ClinicalTrials.gov (NCT06270641) on February 21, 2024, before enrolling the first participant. Figure 3 provides the study design and participant flow.

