#### Post 12-Week Intervention Period

Participants in the ExerciseRx app group are allowed to continue using the ExerciseRx app and encouraged to continue with physical activity goals, as indicated. Their providers may also continue using the provider dashboard of the ExerciseRx platform with their patients.

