### Assessment Procedures and Measures

#### Overview

All participants complete baseline and outcome assessments using REDCap, a web-based data capture platform [28] that can be completed by any digital device with internet access. It includes a human verification service (reCAPTCHA) to avoid responses from bots. Outcome assessments are collected at baseline, post a 12-week treatment period (primary end point), and at a 3-month follow-up after the treatment period. We obtain step count data from all participants throughout the trial and collect data from all randomized participants, regardless of their adherence to treatment (ie, intent-to-treat). Participants receive up to US $150 remuneration for completing the REDCap assessments (US $50 for each assessment point).

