#### Primary Outcome: Step Count

For the week before (baseline) and throughout the 12-week intervention period, step count will be measured within the ExerciseRx app, which passively collects step count data from device sensors using Core Motion, Google Fit, and Google Health Connect. Participants in the usual care condition will also have their step count passively monitored via the ExerciseRx app on their smartphones. Step count is an ideal primary outcome in physical activity promotion trials because it provides an objective, quantifiable measure of daily activity that is sensitive to change and free from self-report bias. It captures both structured and incidental movement, is easy to interpret for participants and clinicians, and is associated with meaningful improvements in health and function [35], including in adults with MS [36,37]. It is possible that step count may be underestimated due to a lack of carrying time or location; a few studies have shown that carrying a phone in a pocket or purse can lead to underestimations of step count [38,39]. However, since this study is looking primarily at changes and trends in step count over time, with consistent phone carrying behaviors, clinically relevant assessments will still be obtained [38,40].

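### The protocol article disagrees on whether app use after week 12 is part of the assigned treatment; as written, the week-26 comparison cannot show that an effect lasts after a 12-week treatment has ended

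*Protocol article*

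**What the plan says.** Several sections of the protocol article bear on how long the intervention lasts.

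- **Abstract, Methods:** "Enrolled participants are assigned to use the ExerciseRx app for 12 weeks, versus a waitlist, usual care control".
- **Design:** outcomes are taken at baseline, after a 12-week treatment period (the primary end point), and "at a 3-month follow-up after the treatment period".
- **Exercise Progression and App Features:** "Participants use the app daily for 25 consecutive weeks after the baseline week". The same paragraph lists what the app shows in that period: step targets and goals, summaries, a weekly survey, educational messages and provider feedback. It mentions no reduction after week 12.
- **Post 12-Week Intervention Period:** "Participants in the ExerciseRx app group are allowed to continue using the ExerciseRx app". Providers may likewise keep using the dashboard.
- **Provider Dashboard and Interactions:** providers act on the dashboard at least weekly during the study period, a term that is not defined there.
- **26-Week Usual Care Period** and **Post Follow-Up Phase:** usual care participants cannot see or use any app feature, and are offered the platform only once the 26-week outcomes have been collected.
- **Introduction (aims):** "Additional secondary analyses will test maintenance of any treatment effects at a 3-month follow-up".

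**The concern.** Daily use over 25 weeks, described as part of the intervention, does not fit with a 12-week treatment followed by a post-treatment assessment. It also does not fit with use that becomes optional after week 12.

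The conflict affects what the last assessment means. A reader told of a 12-week treatment and a later assessment of maintenance will take a week-26 difference as evidence that the gain lasted after treatment stopped. If the app and dashboard are still active in the intervention arm, the same difference may be the effect of treatment that is still being received. These are different claims, and a clinic deciding how long to offer the platform would use them differently.

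**Working it through.** **Inputs.** One baseline week (Baseline Step Count Period). Treatment of 12 weeks (Abstract; Design) or app use of 25 weeks after baseline (Exercise Progression and App Features). Assessments at weeks 13 and 26 (Study Limitations). Control access to the app only after the week-26 outcomes (Post Follow-Up Phase).

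**Step 1: reproduce the calendar.**
- 1 + 12 = week 13, the first post-baseline assessment.
- 1 + 25 = week 26, the final assessment.

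Both durations match the stated assessment weeks. The 25 therefore looks deliberate: it spans the whole interval to the last assessment.

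**Step 2: weeks in dispute.** 25 − 12 = 13 weeks, which is 13/25 = 52% of the longer period. Scheduled exposure before the final assessment differs by a factor of 25/12 = 2.1.

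**Step 3: time off the app before week 26, under each reading.**

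| Reading | Status of weeks 13–25 after baseline | Time off the app before the week-26 assessment |
|---|---|---|
| Daily use for 25 weeks | Part of the intervention | 25 − 25 = 0 weeks |
| 12 weeks, then optional use | Participant's and provider's choice | 0 to 13 weeks, varying by person |

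No section describes the app being switched off in the intervention arm before week 26. The weekly dashboard duty does not settle the matter. If the study period runs to week 26, the duty agrees with the first reading and conflicts with optional dashboard use after week 12.

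**Step 4: what the week-26 contrast compares.** In the intervention arm, access is continued or offered. In the control arm, there is usual care without app features. On either reading the estimate is the effect of access up to week 26. Neither reading gives a planned off-treatment interval common to the intervention arm, which a statement about durability after treatment would need.

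**Step 5: what is not touched.** The primary model covers the 12-week period. The sample size also reproduces:
- Power with 45 per arm, d = 0.60 and two-sided 0.05, normal approximation: Φ(0.60 × √(45/2) − 1.96) = Φ(2.846 − 1.960) = Φ(0.886) = 81.2%. The t-test calculation gives 80.4%. The article states 80%.
- Enrolment: 90/(1 − 0.15) = 105.9, rounded up to 106, as stated.

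Neither figure depends on what happens after week 12.

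**The case against.** The strongest reply is that there is one coherent design with one stray sentence. Assigning the app for 12 weeks and then allowing its use to continue are compatible, and the Design and primary-outcome sections also use a 12-week treatment period. Continued access is openly stated. Maintenance is never defined as durability after withdrawal; whether a week-12 difference persists under continued access is a legitimate question, and because controls wait until after week 26, randomization still protects the comparison. The analyses concerned are secondary, and significant secondary findings are declared hypothesis-generating.

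Much of this stands. The conflict is not between three mutually exclusive durations; it is whether use after week 12 is expected or optional. The week-26 comparison is valid and can test a sustained effect under continued access. What the reply does not remove is the 25-week sentence itself, or the pairing of the word maintenance with an assessment described as coming after the treatment period.

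Four stronger readings are tempting, and the document does not support them:

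- **That step-count collection is also contradictory.** The primary-outcome section says "For the week before (baseline) and throughout the 12-week intervention period, step count will be measured", and the assessment overview says "We obtain step count data from all participants throughout the trial". The first gives the window for the primary outcome and does not say that collection then stops, so the two are compatible.
- **That usual care receives nothing until week 26.** Controls get provider encouragement, possible referrals, a coordinator meeting and the same printed materials. Only the app features are withheld.
- **That the trial plans to conclude that 12 weeks is enough.** No section states or plans that conclusion.
- **That maintenance cannot be tested in any sense.** The limit applies only to durability after treatment ends.

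**Conclusion.** The point holds in limited form. The current text conflicts on whether app and dashboard use in the 13 weeks before the final assessment belongs to the assigned intervention. On either reading, the intervention arm may still be using the app at week 26 while usual care has no app features. The week-26 contrast therefore estimates the effect of continued or offered access versus usual care. Calling it maintenance at a follow-up after treatment would mislabel it if read as durability.

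The label matters for whatever is analysed at the three-month follow-up. That includes the nine symptom and function measures (four symptoms, five functional outcomes), the secondary activity measures, and the moderator analyses that the Introduction plans for that time point. No numerical bias is claimed. The size of the problem is 13 weeks of undefined treatment status, and an off-app interval of 0 weeks or of 0 to 13 weeks.

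The conclusion assumes that no unshown document withdraws the app at week 12; the article describes no such step. It is worth correcting before analysis, but it does not threaten the primary result.

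**What to change.** 1. Reconcile the Abstract, Design, Exercise Progression and App Features, Provider Dashboard and Interactions, and Post 12-Week Intervention Period sections. State whether app and dashboard use in weeks 13–25 after baseline is part of the assigned intervention, and define the study period over which the weekly dashboard duty runs. This review does not choose the duration.
2. If access continues past week 12, label the week-26 analysis as the effect of up to 25 weeks of access versus usual care, that is, a sustained effect under continued access. Do not interpret it as maintenance after treatment has ended.
3. Beside the week-26 estimate, report participant and provider use after week 12. The Implementation Measures section says that the platform records participant logins and survey completion, and provider logins, screen interactions and messages.

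The cost is a few sentences of wording and one descriptive table from logs that the platform keeps. It needs no new visits, measures or participants. The article schedules analysis to begin in January 2026, so the labelling can be settled before then. The price is a more modest claim at week 26.

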#### Provider Dashboard and Interactions

A total of 7 MS providers (2 physiatrists, 4 neurologists, and 1 psychologist) are the providers in this study. Each provider can view on the provider dashboard of the ExerciseRx platform: (1) a triaged aggregate patient panel that depicts their patients’ progress in meeting weekly goals; (2) clinical decision support recommendations for next steps (eg, reactions and message suggestions); and (3) individual participant weekly step count and most common barriers or facilitators (obtained from the surveys completed weekly by participants). The providers check and act on the dashboard at least once a week during the study period. They can offer feedback and reinforcement via the provider dashboard of the ExerciseRx platform, which sends the patient messages via app notifications. For example, if a patient is at less than 75% of their goal by the 3rd week, their MS provider can send them a nudge from the provider dashboard.

#### Low Engagement Support Protocol

The app monitors participants’ engagement and sends automated notifications to the provider and research coordinator. For example, if a patient has not opened the app in 5 days, they receive the following support message: Tech support message #1: “Hello, we noticed you haven’t opened the ExerciseRx app recently. Are you having any difficulties with the app or accessing Wi-Fi or cellular connection? Please let us know if there is anything we can assist you with.” The research coordinator monitors the responses and patient inquiries and provides responses or technical assistance if needed. They also connect the patient to the provider to answer questions as needed; providers can also reach out to participants if they wish.

#### Post 12-Week Intervention Period

Participants in the ExerciseRx app group are allowed to continue using the ExerciseRx app and encouraged to continue with physical activity goals, as indicated. Their providers may also continue using the provider dashboard of the ExerciseRx platform with their patients.

#### Provider Training

The senior author, who helped develop the ExerciseRx platform, and the research coordinator trained the providers on the use of the ExerciseRx platform, including their responsibilities. Although the providers are familiar with the 2020 MS Exercise and Physical Activity Recommendations, [name] (ExerciseRx project lead and sports medicine provider) and [name] (MS physiatrist with exercise expertise) reviewed the guidelines with the providers and described National MS Society and other MS-specific resources (eg, website links and handouts videos) available to providers in educating their patients about the benefits of physical activity in MS.

### Usual Care

#### Overview

The American Academy of Neurology has recommended that patients with MS be counseled by their providers on the benefits of exercise and appropriate physical activity [18]. Participants allocated to usual care receive the care they would normally obtain at the MS Center, including encouragement to participate in and increase physical activity as tolerated from their clinical provider (neurologist, physiatrist, or rehabilitation psychologist), but without the use of the ExerciseRx platform. Specific physical activity guidance varies based on the provider but may include guidance on current exercise recommendations for people with MS (dose, duration, and type), known benefits of exercise in people with MS, links with exercise resources, and referrals to physical therapy or physiatry. In addition, at the beginning of the study intervention period, all participants (including usual care) are given a handout that describes the current physical activity recommendations for adults with MS (type, duration, and intensity), the benefits of physical activity, and links to local and web-based resources suitable to MS (eg, free web-based exercise videos, National MS Society exercise or physical activity educational materials, and links to community resources). We selected the usual care control as a comparator because clinical trials methodologists [34] argue that usual care and waitlist controls are appropriate for efficacy trials when the goal is to promote innovation and test potentially efficacious interventions.

